### Secondary analysis: time-by-treatment interaction

To test whether the intervention effect varies over time, we will include interaction terms between treatment and period. As no clusters are treated in Year 0 (baseline) and all are treated in Year 2, we parametrize the model with interaction terms and period fixed effects.

$$\begin{aligned}&logit(P(Y_{ijk}=1))\\ \quad \quad \quad \quad \quad & =\beta_0+\gamma_1 1\{k=1\}+\gamma_2 1\{k=2\} \\\quad \quad \quad \quad \quad &+ \beta_{11}(Treatment_{jk}\times 1\{k=1\}) \\\quad \quad \quad \quad \quad &+ \beta_{12}(Treatment_{jk}\times 1\{k=2\})\\\quad \quad \quad \quad \quad &+X_{ijk}^T\beta_2+u_j\end{aligned}$$

$$\beta_{11}$$ and $$\beta_{12}$$ are treatment effects (log-odds) in Year 1 and Year 2 respectively. We will conduct additional analyses for which we have no directional hypothesis or preliminary data to guide sample size considerations. Analyses of our secondary outcomes listed in Table 2 (e.g., specific vaccines, vaccination attitudes) will use analogous GLMMs appropriate to the outcome type. We will also conduct mediation analyses, to ascertain if the secondary outcomes are on the mediation pathway between the experimental conditions and the primary outcome. We will also do subgroup analysis based on individual-level characteristics (e.g., age, gender, baseline covariates). All data will be analyzed in R or SAS.

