The first group had 12 districts, and the second six districts. For the first 12 districts, we additionally removed six districts whose population center was close to the population center of another district to avoid spillovers. In this way, we ended with six districts in each group. We then randomly assigned the two groups to either the MVC strategy or the religious conference strategy. Thus, the six districts from the first group were assigned to the MVC strategy, and the six districts in the second group were assigned to the religious conference strategy (Table 1). For each group of 6, 3 districts were from Banda Aceh, and 3 from Aceh Besar. Within each group, we then randomized three districts to begin the intervention in year 1 and three in year 2 using a computer-generated allocation. District authorities were informed only after randomization. Although the strategies were implemented simultaneously, analytically, these are treated as two separate trials. The stepped wedge design and the district schedule for the two interventions are depicted in Fig. 1 and Table 1.

**Table 1 Tab1:** Sites of the two interventions, TABRIE, Aceh, Indonesia, 2023–2025

Strategy	Year(s) of intervention (randomized)	Location	District
Mobile vaccine clinic (MVC)	1 and 2	Banda Aceh	Baiturrahman
MVC	1 and 2	Banda Aceh	Jaya Baru
MVC	1 and 2	Aceh Besar	Mesjid Raya
MVC	2	Banda Aceh	Kuta Raja
MVC	2	Aceh Besar	Peukan Bada
MVC	2	Aceh Besar	Krueng Barona Jaya
Religious conference	1 and 2	Aceh Besar	Kuta Malaka
Religious conference	1 and 2	Aceh Besar	Darussalam
Religious conference	1 and 2	Banda Aceh	Meuraxa
Religious conference	2	Banda Aceh	Kuta Alam
Religious conference	2	Banda Aceh	Lueng Bata
Religious conference	2	Aceh Besar	Montasik

Year of intervention start was randomized within each intervention arm (3 districts began in year 1 and 3 in year 2)

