### Mixed-effects logistic regression for preliminary treatment effects

Fit a binary outcome model with a cluster-level random effect (to account for intracluster correlation)

where:*i*: individual, j: cluster, w *k∈ {0,1,2}: year*$$Treatmen{t}_{jk}$$: indicator variable for treatment status in cluster j in year k$$NA$$$${X}_{ijk}$$: covariates listed above$${u}_{j}$$: cluster-level random intercept$$logit(P({Y}_{ijk}=1))={\beta }_{0}+{\beta }_{1}\cdot Treatmen{t}_{jk}+\gamma_{1}1\{k=1\} +X_{ijk}^T{\beta }_{2}+{u}_{j}$$

Here $${\beta }_{1}$$ is the log-odds ratio for the preliminary treatment effect.

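### The Year 2 treatment effect in the time-by-treatment model cannot be estimated, because every district is treated in Year 2

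*Protocol article*

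**What the plan says.** In the protocol article, the section on the time-by-treatment interaction (under Statistical methods {20a}) gives the aim: "To test whether the intervention effect varies over time, we will include interaction terms between treatment and period". It then gives the reason for the form of the model: "As no clusters are treated in Year 0 (baseline) and all are treated in Year 2". Both period effects are kept next to the two interaction terms. The linear predictor, apart from covariates and the district random intercept, is

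β0 + γ1·1{k=1} + γ2·1{k=2} + β11·(Treatment × 1{k=1}) + β12·(Treatment × 1{k=2}),

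and β11 and β12 "are treatment effects (log-odds) in Year 1 and Year 2 respectively".

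Three other statements fix what the columns contain:

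- Treatment is defined in the interim-analysis section as an "indicator variable for treatment status in cluster j in year k".
- Trial design {8} says that within each group of six, "we then randomized three districts to begin the intervention in year 1 and three in year 2". Table 1 lists every district as treated either in both years or in year 2.
- The same section says of the two strategies that "analytically, these are treated as two separate trials", so each model is fitted to 6 districts × 3 surveys.

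**The concern.** A treatment effect in a given year needs treated and untreated districts in that year, or an assumption that supplies the missing comparison. Year 2 has no untreated districts, and the model gives Year 2 its own free period effect, so nothing is left to identify β12. The article offers full treatment in Year 2 as the reason for this parametrization, when that fact is what makes it fail.

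At stake is a prespecified coefficient with a causal label. Depending on software and column order, the analyst may get a singular-fit message, no Year 2 estimate, or a number called the Year 2 treatment effect that is really the before-and-after change since 2023. Any secondary outcome analysed with this model would have the same problem. Both interventions are repeated each year, so whether the effect holds or builds in a second year is a real question that this model cannot answer.

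**Working it through.** **1. The plan's own figure.** Sample size {14} gives 49.5% against 62.5%, ICC 0.0816, 100 per cluster and power 0.80. I read 100 as per district per survey, with two-sided 5%. Using the mean proportion 0.56, the total variance is 0.56 × 0.44 = 0.2464. Then τ² = 0.0816 × 0.2464 = 0.02011, and the sampling variance of a district-year mean is σ² = 0.9184 × 0.2464 / 100 = 0.002263.

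The Hussey-Hughes variance for the primary model is I·σ²(σ² + Tτ²) / [(IU − W)σ² + (U² + ITU − TW − IV)τ²], with I = 6, T = 3, U = 9, W = 45, V = 15:

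- numerator: 6 × 0.002263 × 0.06258 = 0.000850
- denominator: 9 × 0.002263 + 18 × 0.02011 = 0.3823
- SE = √0.002223 = 0.0471; power = Φ(0.13/0.0471 − 1.96) = 0.787

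This is close to the stated 0.80, so the layout and inputs are read as intended.

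**2. The planned interaction model.** Rows for one trial:

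| Districts | Year | 1{k=2} | Treatment | Treatment × 1{k=2} |
|---|---|---|---|---|
| 3 early | 0 | 0 | 0 | 0 |
| 3 early | 1 | 0 | 1 | 0 |
| 3 early | 2 | 1 | 1 | 1 |
| 3 late | 0 | 0 | 0 | 0 |
| 3 late | 1 | 0 | 0 | 0 |
| 3 late | 2 | 1 | 1 | 1 |

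The third and fifth columns are the same.

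- The design has 5 columns and rank 4 (10 columns and rank 9 with district dummies).
- The null vector is γ2 minus β12.
- Set beside the primary model's matrix, the rank is still 4, so the interaction model is the primary model relabelled.
- Pooling all 12 districts does not help: 5 columns and rank 4 with one treatment indicator, 7 columns and rank 6 with separate indicators for the two strategies.

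**3. Likelihood check.** In simulated data, (γ2, β12) = (0.2, 0.53), (0.73, 0), (−1.27, 2) and (2.73, −2) all give log-likelihood −1138.971793.

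**4. Size of the error if γ2 is dropped.** Assume a secular rise of 5 points from 49.5% to 54.5%: ln(0.545/0.455) − ln(0.495/0.505) = 0.20 log-odds. The planned effect is ln(0.625/0.375) − ln(0.495/0.505) = 0.53. The model would report 0.20 + 0.53 = 0.73, an odds ratio of about 2.08 instead of 1.70. With no true effect it would report 0.20, the trend alone.

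**5. What can be estimated.** Let d0, d1, d2 be the early-minus-late differences in Years 0, 1 and 2.

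- Planned model: the expected differences are 0, β11, 0. β12 cancels from every between-district comparison.
- Exposure-time model, with δ1 and δ2 for the first and second year of exposure: the expected differences are 0, δ1, δ2 − δ1. The design has rank 5 of 5 (10 of 10 with district dummies).

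With ρ = τ²/(τ² + σ²) = 0.899, the estimate of δ1 is d1 − ρd0 and that of δ2 − δ1 is d2 − ρd0:

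- each has variance (2/3)(0.02237)(1 − 0.899²) = 0.00286, so SE 0.054
- their covariance is (2/3)(0.02011)(1 − 0.899) = 0.00136
- δ2 is their sum: variance 2 × 0.00286 + 2 × 0.00136 = 0.0084, so SE 0.092

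For the test of δ1 = δ2, 80% power needs (1.96 + 0.84) × 0.0535 = 0.15, or 15 points. These SEs use a linear-probability approximation without covariates.

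**The case against.** The algebra cannot be contested: the article prints the equation and interprets the coefficient, so this is neither condensation nor a detail left to an analysis plan. The fair objections concern weight and remedy.

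- **It is a secondary analysis.** The primary model is full rank, the sample size does not rest on the interaction model, and β11 is estimable. This stands and limits the damage.
- **Software may flag the problem.** R or SAS may warn, set a coefficient to zero or report a singular fit, so a misleading number is one possible outcome and not a certainty. This stands. The bias in step 4 applies only if γ2 is the term dropped.
- **Secondary outcomes may be unaffected.** The analogous models promised for them could be analogous to the primary model. This stands; the problem spreads only where the interaction model is used.
- **Jaya Baru cooperated only partly in year 2.** Coding it untreated in Year 2 would restore full rank. The article does not plan this, and the contrast would rest on one non-randomised district. The planned leave-one-out analysis still leaves every remaining district treated in Year 2. This does not rescue β12.
- **The remedy answers a different question.** Exposure time is not calendar time, and the replacement assumes that the first-year effect is the same in 2024 for early districts and in 2025 for late ones. This stands and must be stated with the fix.

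**Conclusion.** The concern holds. As written, β12 is not a Year 2 treatment effect and cannot be estimated, and the test of variation by calendar year does not exist (rank 4 of 5, zero degrees of freedom beyond the primary model). This follows from the roll-out alone; sample size, covariates and the random intercept do not alter it. It assumes only that treatment is coded at district level by year, as the article defines it. The possible bias equals the full secular change from 2023 to 2025 on the log-odds scale, if γ2 is the term dropped; the 5-point trend used above is an assumption. The primary analysis is still estimable, but a causal label on this coefficient should be removed before the data are analysed.

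**What to change.** Replace the two interaction terms by δ1·1{first year of exposure} + δ2·1{second year of exposure}, keeping γ1, γ2, the covariates and the district random intercept, and test δ1 = δ2. Alongside it, state that:

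- a calendar Year 2 effect against control is not estimable in this design;
- δ1 and δ2 assume the same first-year effect in both calendar years;
- the test is exploratory: its SE is about 5 points, so it needs a difference of about 15 points for 80% power, more than the 13 points the trial is sized for, and six districts per trial make the normal approximation optimistic.

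The simpler alternative is to delete the β12 term and say that variation by calendar year cannot be tested. What remains is then the primary model, with β11 in place of β1. Whichever is chosen should also apply to any secondary outcome that would have used the interaction model.

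The cost is one equation, a few sentences and the matching code. No further data are needed. The price of the exposure-time model is precision: SE about 9 points for δ2 and about 5 for δ1.

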### Outcomes {12}

The primary outcome is full vaccination, which is ascertained through records from vaccination cards or clinic records. Secondary outcomes are also listed in Table 2, along with the original measure in the survey instrument, and how it is re-coded (as applicable).

**Table 2 Tab2:** Primary and secondary outcome measures

**#**	**Description**	**Measurement**	**Recode**
Primary outcome			
1	Full vaccination	Records from vaccination cards or clinic records 6 months since the start of the intervention: 1 dose of BCG; 3 doses of DTP; 3 doses of polio vaccine; 1 dose of measles-containing vaccine	
Secondary outcomes			
2a	DTP dose 1 vaccination	Records from vaccination cards or clinic records	
2b	Measles dose 1 vaccination	Records from vaccination cards or clinic records	
2c	Vaccine hesitancy	Overall, how hesitant about childhood shots would you consider yourself to be ● Not at all hesitant (1) ● Not that hesitant (2) ● Somewhat hesitant (3) ● Very hesitant (4) ● Unsure (5) ● Refused (6)	Dichotomized (3 + 4 is hesitant, other responses and missing responses count as non-hesitant)
2d	Social norms of vaccination	Do you think most parents you know vaccinate their children? ● Yes (1) ● No (2) ● Don’t know (3)	Dichotomized (1 is yes, other responses and missing responses count as no)
2e	Trust in community health workers	How much would you trust your child being vaccinated by a community health worker in a mobile vaccine clinic? ● Strongly distrust (1) ● Distrust (2) ● Neither trust or distrust (3) ● Trust (4) ● Strongly trust (5)	Dichotomized (4 + 5 is trust, other responses and missing responses count as do not trust)
2f	Distance barrier	What barriers have you encountered in getting your children vaccinated? (Select all that apply) ● [Other options provided] ● The distance from my residence to the vaccination site is too far (6)	Dichotomized (selecting 6 is yes, other responses and missing responses count as no)
2g	Vaccination norms from religious leaders	Do you think your religious leaders want you to vaccinate your children? ● Yes (1) ● No (2) ● Don’t know (3)	Dichotomized (1 is yes, other responses and missing responses count as no)
2h	Information from religious leaders	How and where did you hear information about the vaccination program for your children? (Select all that apply) ● [Other options provided] ● From religious leaders (6)	Dichotomized (selecting 6 is yes, other responses and missing responses count as no)

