### Participant timeline {13}

Cross-sectional surveys will be conducted September of each year from 2023 to 2025. Baseline year is 2023, year 1 of the interventions is 2024, and year 2 is 2025. In each year, a religious conference will be held in January. We expect that participants will disseminate vaccine promotions to their communities after this date. We will also follow up with participants from the conference in March and June. For the MVCs, community health workers will conduct outreach events in two rounds. Round 1 will be in January and February, and round 2 will be in May and June (Fig. 2).

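### The planned mediation analysis admits DTP dose 1 and measles dose 1 as mediators of an outcome they are part of, and the other candidate mediators have no established time order

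*Protocol article*

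**What the plan says.** In the protocol article, the section on the time-by-treatment interaction plans mediation analyses "to ascertain if the secondary outcomes are on the mediation pathway between the experimental conditions and the primary outcome". It does not narrow the set. The sentence before it refers to the Table 2 secondary outcomes and gives specific vaccines as well as attitudes as examples.

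Under Outcomes {12}, Table 2 defines full vaccination as "1 dose of BCG; 3 doses of DTP; 3 doses of polio vaccine; 1 dose of measles-containing vaccine". Secondary outcomes 2a and 2b are "DTP dose 1 vaccination" and "Measles dose 1 vaccination", taken from the same type of record as the primary outcome.

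Outcomes 2c to 2h are questions put to the parent, for example "Overall, how hesitant about childhood shots would you consider yourself to be" (2c). Participant timeline {13} says: "Cross-sectional surveys will be conducted September of each year from 2023 to 2025". The mobile clinic runs earlier in the year: "Round 1 will be in January and February, and round 2 will be in May and June". The conference is held in January, with follow-up in March and June. Sampling is repeated cross-sectional, so no parent has an earlier value of the candidate mediator.

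**The concern.** A mediator should be a distinct step through which the intervention changes the outcome. DTP dose 1 and measles dose 1 are not distinct from full vaccination; they belong to its definition. A sizeable indirect effect through measles vaccination would mean only that children who became fully vaccinated also received a vaccine that full vaccination requires. It could still be read as evidence of mechanism.

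For 2c to 2h the difficulty is time order. The outcome consists of doses already on record, whereas the questions are asked afterwards. Having a child vaccinated, or having met the mobile clinic, can change what a parent says about hesitancy or trust. The association may therefore run from outcome to supposed mediator.

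**Working it through.** The article gives no mediation figure to reproduce. Its Sample size {14} section supplies the two coverages used here: 49.5% in controls and 62.5% under intervention, a 13-point difference. It gives no measles coverage for the study districts, so that input is assumed and varied.

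**Step 1: the definition.** Let Y be full vaccination and M the measles dose. Table 2 requires M for Y, so P(Y=1 | M=0) = 0 in both conditions. The same holds for DTP dose 1.

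**Step 2: the built-in indirect effect.** On the risk-difference scale,

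indirect effect = (rise in P(M)) × [P(Y | M=1) − P(Y | M=0)].

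The last term is zero, and P(Y | M=1) = P(Y)/P(M). With control measles coverage assumed at 60%, this is 0.495/0.60 = 0.825. Treated measles coverage cannot be below 62.5%, so the smallest possible rise from 60% is 2.5 points.

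| Assumed control measles coverage | Assumed rise | Indirect effect | Share of 0.13 |
|---|---|---|---|
| 60% | 2.5 points | 0.025 × 0.825 = 0.0206 | 16% |
| 60% | 5 points | 0.05 × 0.825 = 0.0413 | 32% |
| 60% | 13 points | 0.13 × 0.825 = 0.107 | 82% |
| 65% | 0 | 0 | 0% |

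Using the treated-arm conditional probability instead changes the first three shares only modestly:

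- 2.5 points: 0.625/0.625 = 1.000, share 19%
- 5 points: 0.625/0.65 = 0.962, share 37%
- 13 points: 0.625/0.73 = 0.856, share 86%

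**Step 3: cross-check by simulation.** This used 2,000,000 individuals without clustering and assumed dose-uptake parameters, which were not calibrated to the 13-point effect.

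- If the intervention raises all doses through one common propensity, about 39% of the effect is attributed to DTP dose 1 and about 58% to measles.
- If it acts only on completing the later doses, both shares are 0%.

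**Step 4: reverse causation for 2c to 2h.** Suppose an attitude has no causal role and only follows from vaccination. Let P(favourable) be 0.60 in parents of children not fully vaccinated and 0.80 in parents of fully vaccinated children.

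- Favourable, control: 0.495 × 0.80 + 0.505 × 0.60 = 0.699
- Favourable, intervention: 0.625 × 0.80 + 0.375 × 0.60 = 0.725
- Rise: 0.026
- Intervention, P(Y | favourable) = 0.500/0.725 = 0.690 and P(Y | not favourable) = 0.125/0.275 = 0.455, difference 0.235
- False indirect effect: 0.026 × 0.235 = 0.0061, or about 5% of 0.13

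The simulation agrees. It gives about 10% with 0.50 versus 0.80, and about 22% with 0.40 versus 0.85. These attitude probabilities are assumptions.

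**The case against.** The strongest defence is that this is one exploratory sentence in a condensed article. The secondary objectives are declared exploratory, and the additional analyses are introduced as having no directional hypothesis. Mediator models and identifying assumptions would normally sit in a fuller document. That stands for the choice of estimator and the assumptions. It does not cover the mediator set, which the article itself fixes: a plan that followed the sentence would include 2a and 2b.

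For DTP dose 1 it can also be said that the first dose precedes the third, so separating starting the series from completing it is interpretable. That is fair as a description of which doses moved. It remains a split of the outcome into its parts and is not evidence about how either strategy works.

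A reader might go further and infer that the analysis will return large, precise mediated proportions whatever the true mechanism. The documents do not support this. The share varies with how far the intervention moves each dose and can be zero. The false share for an attitude was 5% to 22% under the assumptions tried. With six districts per trial there is no ground for expecting precision, and the article does not promise a proportion mediated.

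Nor are 2c to 2h all current attitudes: 2f and 2h ask about past barriers and past sources of information. For those the order relative to the doses is unknown, which is weaker than known to be reversed.

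**Conclusion.** The point holds for 2a and 2b as a matter of definition, with no assumption needed: full vaccination is impossible without either dose, so any intervention effect on them passes into an indirect effect by construction. How large that would be is not determined by the documents. Under the assumed coverages it runs from 0% to about 82% of the 13-point effect for measles, depending on the rise in measles coverage.

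For 2c to 2h the conclusion is narrower. One survey, after the recorded doses, leaves time order undetermined and reverse causation possible. That justifies a stated limitation. A reader might infer that no indirect effect should ever be estimated for these items, but statisticians can reasonably differ on that and the documents do not settle it.

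The primary treatment-effect estimate, the sample size and the planned intervention effects on each secondary outcome are unaffected.

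**What to change.** Amend the mediation sentence to exclude 2a and 2b from the mediators. Their intervention effects are already planned as secondary analyses, so what the trial learns about these doses is kept.

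For 2c to 2h, add that each is measured once, in the same September survey and after the recorded doses; that the time order is therefore undetermined and reverse causation possible; and that any mediation result will be reported as an exploratory concurrent association and not as evidence of mechanism.

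The cost is a sentence or two of text and fewer exploratory analyses.

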### Interim analyses {21b}

We will assess the preliminary effect of the intervention while preserving trial integrity.

### Descriptive analysis

Summarize outcomes (proportion with binary outcome) by cluster for baseline year and year 1.Compare intervention vs. control clusters descriptively at the end of year 1.Summarize key baseline individual- and cluster-level covariates by treatment group (for treated clusters) and control group (for untreated clusters at year 1).

### Mixed-effects logistic regression for preliminary treatment effects

Fit a binary outcome model with a cluster-level random effect (to account for intracluster correlation)

where:*i*: individual, j: cluster, w *k∈ {0,1,2}: year*$$Treatmen{t}_{jk}$$: indicator variable for treatment status in cluster j in year k$$NA$$$${X}_{ijk}$$: covariates listed above$${u}_{j}$$: cluster-level random intercept$$logit(P({Y}_{ijk}=1))={\beta }_{0}+{\beta }_{1}\cdot Treatmen{t}_{jk}+\gamma_{1}1\{k=1\} +X_{ijk}^T{\beta }_{2}+{u}_{j}$$

Here $${\beta }_{1}$$ is the log-odds ratio for the preliminary treatment effect.

